### **Visit 3 – Day 8**

Visit 3 will take place at the 1.5T scanner of the SPMMRC and will last up to 1 hour. Participants should attend at 8am (first scan session) or 9am (second scan session). They should not eat or drink after waking, except a small sip of water for essential tablets.

Participants will return their 24 hour urine collection. This will be weighed and aliquots taken for metabolomic analysis. They will also return their food diary. During their visit participants will undergo 2 procedures:

- A test of breath hydrogen and methane using the GastroCheck meter (Bedfont, UK)
- A sequence of MRI scans (15-20 minutes)

The exact order of procedures may vary. Prior to the MRI scans participants will change into surgical scrubs (provided) and confirm the MRI safety screening questionnaire. The MRI scan sequences will measure colonic volume, colonic gas volume and other MRI parameters ( $T_1$ ,  $T_2$ ) that describe physico-chemical characteristics of the bowel and its contents.

After all procedures have been completed participants will be given a low FODMAP breakfast and their study supplement. The supplement will be either/ or:

- A. Maltodextrin (the Hut Group, Northwich)
- B. Oligofructose as OrafitP95® (Beneo, Germany)

Participant should take 7 grams (= one scoop) of supplement twice daily for a week. The supplement should be added to a warm/ hot drink and stirred. Participants will take their first serving of study supplement at the SPMMRC to ensure there are no issues with preparation or consumption. Participants should follow a low FODMAP diet until their next MRI scan.

Participants will take away from the visit:

- A second food diary to complete over the next week
- A second stool collection kit

### **Days 8 – 13**

During days 8 – 13 participants should adhere to the low FODMAP diet. The study team will attempt to contact participants at least once during that time to discuss any issues arising and offer encouragement, and participants will be free to contact the study team with any issues that arise.

Participants should collect a second set of stool samples during the two days before Visit 4, in the same manner as described before Visit 2. They should abstain from alcohol from 8am on Day 13 (48 hours before the MRI scan).

### **Visit 4 – Day 14**

Visit 4 will take place at the NDDC and last 15 - 20 minutes. As for Visit 2, participants should fast until they attend around 8.30am. Stool and urine samples will be collected. Participants can return their low FODMAP advice booklets at this visit or Visit 5. The food diary should be continued until Visit 5.

Participants will be provided with a low FODMAP breakfast and asked to swallow 5 transit

markers. They should continue to take their supplement for the rest of the day. The last serving of supplement should be the second serving on Day 14.

At the end of the visit participants will take away:

- A 24-hour urine collection bottle containing boric acid, with equipment to allow collection
- A low FODMAP packed lunch
- A low FODMAP meal for evening consumption

Participants may snack in addition to the meals provided but should use the food supplied for their main meals. They should continue their food diaries until the next morning. After 10pm that night no food should be eaten and only water should be drunk.

### **Visit 5 – Day 15**

Visit 5 will take place at the 1.5T scanner of the SPMRC and will last up to 1 hour. As for Visit 3 participants should attend at 8am (first scan session) or 9am (second scan session). They should not eat or drink after waking, except a small sip of water for essential tablets.

They will return their second urine collection and food diary, along with any outstanding information booklets. They will also return their supplement container to allow weighing for compliance.

Participants will then undergo the same procedures as for Visit 3: breath testing and MRI scanning. The completion of these procedures will be the end of the participant's involvement in the trial. They will be offered a light snack and a drink.

### **Compliance**

Supplement compliance will be assessed by measuring the gross weight of the supplement container at the start and end of the week. Compliance will be calculated as (actual weight change / expected weight change) \* 100%, with an acceptable range of 70 – 140%.

Dietary compliance will be assessed by food diary. No specific compliance parameters will be pre-specified but FODMAP intake will be compared between groups. To allow for tail-off and omission in reporting analysis will be done on the four days with highest calorie intake.

### **Transport and Storage of Tissues**

Samples will be stored in linked anonymised format at the NDDC and labelled using a combination of date of birth, initials and study number to permit accurate linkage to the case report form and consent form.

Samples will be stored in -80C freezers. Essential maintenance of the laboratory space and equipment is performed by two laboratory technicians. The master database will be held by the Chief Investigator in a password encrypted file.

Once analysis has taken place, samples will be stored within the Research Tissue Bank for future research (DI [name] Licence Number 12265) if participants are agreeable and sign the optional clause on the consent form. Where participants do not agree to the future use of the samples they will be destroyed in accordance with the Human Tissue Act, 2004.

# Laboratory Analysis

## MRI Scanning Schedule

Subjects will be scanned on a research dedicated 1.5T Philips Achieva MRI scanner, using a parallel imaging SENSE 16-element torso coil. A range of MRI sequences will be used to image the abdomen including:

- 1) A T1 weighted 3D turbo field echo (TFE) sequence (repetition time (TR) = 4.0 ms, echo time (TE) = 1.9 ms, flip angle (FA) 10°, acquired resolution (AQR) 2.3 x 2.3 x 5 mm^3) will be used to locate and count the number of transit marker pills remaining in the colon at 24 and 48 hours. A multi shot T1 weighted TFE sequence with fat suppression (TR = 2.7 ms, TE = 1.4, AQR 1.8 x 2.6 x 3.6 mm^3, sensitivity encoding (SENSE) factor = 2.0) will be used to create a movie which will allow colonic rotation and give 3D visualisation of the colon. This will further clarify the location of the marker pills.
- 2) A high resolution bTFE sequence to acquire images of the contents of the ascending colon (TR = 3.1 ms, TE = 1.56 ms, acquired resolution = 1.50 mm x 1.50 mm, reconstructed resolution = 0.86 x 0.86, 8 slices 5 mm thick, up to 5.0 mm gap to cover whole ascending colon, flip angle 45°).
- 3) We will assess T1/ T2 of colonic contents using previously published methods.

Depending on the sequence, each image set will be acquired with an expiration breath-hold between 13 and 24 seconds, monitored using a respiratory belt. Subjects will spend approximately 15 minutes inside the magnet.

## Whole gut transit

This will follow the method described in Chaddock et al. Transit will be assessed and scored from the scans performed 24 hours after marker ingestion. The previously documented scoring system divides the bowel into 8 sections, (Figure 1A) allowing each capsule to be scored according to its position in the bowel after 24 hours. A weighted average position score of the 5 pills (Figure 1B) is determined for each volunteer.

[figure not shown]

**Figure 1: (A)** Scoring system **(B)** an examples of maximum intensity from a volunteers T1-weighted TFE sequence scan 24 hours after swallowing 3 transit capsules showing the position of the capsules (indicated also by the red arrows) within the gut. On these sequences the capsules appear bright and in this case two can be seen in the ascending colon and 1 in the descending colon.

## **Colonic Morphology**

Colonic volume will be calculated followed the method described recently by Pritchard et al. Individual regional colon volumes will be manually segmented from the coronal data on each image slice using Analyze9™ software (Mayo Foundation, Rochester MN, USA). Each colon region will be identified within each coronal image slice, building a 3D representation of the morphology from which the volume of each region is measured. Information from axial data will be used to guide definition of the regions where anatomy is ambiguous.

## **Urinary Metabolomics**

This will be done in the Centre for Analytical Biosciences at the School of Pharmacy, under the supervision of [name]. Urine will be analysed using a validated direct infusion mass spectrometry method involving high resolution accurate mass analysis. This will enable the analysis of changes in levels of more than 35 compounds naturally found in urine including those linked with bacterial metabolism.

## **Stool**

Stool samples will be stored until additional funding is confirmed. The intention will be to test stool microbiota using semi-quantitative PCR, using primers derived from a comprehensive study of the effects of OF on the microbiota. Where this work involves NHS staff and premises a separate ethics submission will be made.

Stool will also be tested for short-chain fatty acid content. This will be done in the NDDC under the supervision of [name] using gas chromatography – mass spectrometry (GC-MS).

## **STATISTICS**

### **Sample Size and justification**

We will recruit up to 45 participants in order to gather 36 complete data sets.

Our pilot data found an 18% increase in colonic volume after normal diet was supplemented with OF. The null hypothesis would be that there is no change in colonic volume in either arm of the planned study (OF or maltodextrin). The effect of the low FODMAP diet is uncertain but should be the same in both arms. If our hypothesis is correct then volume may decrease in the maltodextrin arm.

Data from a previous 4-period crossover study of healthy volunteers found a within-individual coefficient of variation for fasting colonic volume of 17% (unpublished). A sample size of 36, randomised 1:1, would give 80% power to detect a 15% increase in the change in volume between treatment arms ( $\alpha = 0.05$ , 1-tailed). Given our pilot work and the resulting study hypothesis we feel that a 1-tailed test is appropriate. Given the mechanistic nature of the study withdrawals and dropouts will be replaced.

Data will be assessed for normality using the Shapiro-Wilk test and other such methods as appropriate. Where normally distributed, endpoints will be assessed using parametric methods. The primary outcome measure will be analysed by t-test to compare the primary

endpoint between groups. Where the data is not normally distributed, non-parametric methods will be used.

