### **Primary endpoint**

- Percentage change in fasting colonic volume after one week of dietary intervention as measured by MRI

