### **Randomisation and Blinding**

Participants will be allocated to a treatment group according to a randomization schedule generated by an independent member of staff at the SPMMRC or NDDC using the online program [www.randomization.com](http://www.randomization.com). Randomization will be 1:1 in blocks of 6 to prevent imbalance between groups.

Participants, investigators and analysts will be blind to treatment allocation until analysis of the primary and secondary endpoints is complete. The intervention supplements are both white powders which are indistinguishable. They will be supplied in opaque containers with the gross weight recorded on the side. Labelling will be completed by members of NDDC/ SPMMRC staff not directly involved with the study.

The code will be kept by the Chief Investigator in a sealed envelope and on a password

protected computer not accessible by the study team. No adverse events directly relating to the study product are expected. Should a serious adverse event occur the intervention will be discontinued without any need to unblind as the supplement will have no bearing on subsequent management.

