## Details of Trial Regimen

This study will use a parallel group design with 18 subjects per group.

### Visit 1 (Consent) – Day 0

Visit 1 will take place at the NDDC and last 20-30 minutes. After consent has been obtained participants will be screened against eligibility criteria will be enrolled if they are eligible. An MRI safety screening questionnaire will be completed as part of this process. A record will be taken of height, weight, current medication and any medical conditions and smoking history.

Participants will then fill in a food frequency questionnaire, the Comprehensive Nutrition Assessment Questionnaire (CNAQ), a questionnaire validated in an antipodean population to assess FODMAP content of the diet. This is pilot work to look at the utility of the CNAQ in a UK population.

Participants will then be instructed in how to complete a one week food diary. The first day of the food diary will be designated Day 1. They will also be told how to collect a stool sample.

They will be given to take away:

- A one week food diary based on the EPIC food diary, with guidance
- A stool collection kit including gloves, a cardboard tray and sample pots, with instructions

The stool collection kit has been used extensively in other departmental studies. A microbiology container that meets UN3373B standards for transport (Biobottle™; see picture) will be provided, along with a freezable gel pack. Participants will be asked to freeze the gel pack and collect 3 cherry-sized aliquots of stool from a single motion. This should be done at some point in the two days before Visit 2. Once collected, sample tubes can be put in the Bio-Bottle™ along with the gel pack and stored in the home freezer until visit 2.

[figure not shown]

Participants should not take excessive alcohol during the study and should abstain from alcohol from 8am on Day 6 (48 hours before the MRI scan).

### Visit 2 – Day 7

Visit 2 will take place in the NDDC and last around 90 minutes. Participants will attend around 8.30am, and will fast until they attend except for a small amount of water with essential tablets. They will return their stool samples, which will be immediately transferred to the -80C freezers of the NDDC. They will provide a urine sample which will be spun and frozen. Having emptied their bladders, participants will be asked to start a 24 hour urine collection.

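### The claimed 80% power treats the 17% CV of a single colonic volume as the SD of a change; on the protocol's own inputs, 36 participants give about 58% at best

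*Protocol*

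**What the plan says.** The Sample Size and justification section reports that an earlier 4-period crossover study in healthy volunteers "found a within-individual coefficient of variation for fasting colonic volume of 17% (unpublished". It then claims: "A sample size of 36, randomised 1:1, would give 80% power to detect a 15% increase in the change in volume between treatment arms", with alpha 0.05. On sidedness it says "we feel that a 1-tailed test is appropriate". No other variability figure appears: there is no SD of a change, no correlation between visits and no formula.

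The quantity to be tested is defined under Primary endpoint as "Percentage change in fasting colonic volume after one week of dietary intervention as measured by MRI". The scans are at Visit 3 (Day 8) and Visit 5 (Day 15). Details of Trial Regimen fixes the arm size: "This study will use a parallel group design with 18 subjects per group". The analysis compares the percentage change between the two arms: "The primary outcome measure will be analysed by t-test to compare the primary" endpoint between groups. No baseline covariate is mentioned.

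**The concern.** A power calculation for a two-sample t-test needs the SD, between people within an arm, of the variable being tested. Here that variable is a change between two visits. The protocol supplies the within-person scatter of the volume at one visit. A change is built from two such readings, so under independent errors its variance is twice that of one reading. If 17% was used as though it were already the SD of the change, the stated power is too high.

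The figure at stake supports the sample size for the primary endpoint. If it is overstated, those approving the study are told it is more sensitive than it is. A non-significant result would then be taken as the answer of an 80%-powered trial.

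**Working it through.** **Inputs, all from the Protocol.** 18 per arm (Details of Trial Regimen). Difference 15 percentage points, one-tailed alpha 0.05, within-individual CV 17% (Sample Size and justification). Endpoint: percentage change between two scans (Primary endpoint). Test: two-sample t-test, no covariate.

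**Formula.** Noncentrality = difference ÷ (SD × √(2/n)). With n = 18 this is 3 × difference ÷ SD. Normal-approximation power is Φ(noncentrality − 1.645). The exact version uses the noncentral t with 34 degrees of freedom.

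**Step 1: reproduce the stated 80%.** Enter 17% directly as the SD of the change.

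- Additive scale: 3 × 15 ÷ 17 = 2.647. Power is Φ(1.002) = 84.2%, or 82.9% by noncentral t. For 80% power, 2 × (1.645 + 0.842)² × (17/15)² = 15.9, so 16 per arm by the normal approximation and 17 by t (32 to 34 in total).
- Log scale: difference ln 1.15 = 0.1398, SD √ln(1 + 0.17²) = 0.1688. Noncentrality 2.484, power 79.9% (normal) or 78.5% (t).

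The stated figure is therefore recovered, almost exactly on the log scale. Two-sided versions with the same SD give 67% to 75% and do not recover it.

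**Step 2: the SD of the change.** Two readings with independent errors of 17% each give √(17² + 17²) = √2 × 17 = 24.04%.

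**Step 3: power with that SD, 18 per arm.**

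| Scale | Normal approximation | Noncentral t |
|---|---|---|
| Additive, 15 points, SD 24.04 | 59.0% | 57.5% |
| Log, ratio 1.15, SD 0.2387 | 54.4% | 53.1% |

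On the additive scale the noncentrality is 3 × 15 ÷ 24.04 = 1.872, and Φ(1.872 − 1.645) = 59.0%.

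A simulation of the endpoint as defined (lognormal volumes with CV 17% at each visit, t-test on percentage change, true ratio 1.15, 40,000 trials) gives 52%. The SD of percentage change is then about 25% in one arm and 29% in the other, which is why power falls a little below the additive figure.

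**Step 4: what 36 participants can do.**

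- Difference detectable with 80% power at SD 24.04: 20.3 points.
- Number needed for 80% power at 15 points: 33 per arm by t (66 in total), 32 by the normal approximation; 37 per arm (74) on the log scale.
- SD of change that would give exactly 80% at 15 points: 17.7 by t, 18.1 by the normal approximation. By t this implies a single-scan CV of 17.7 ÷ √2 = 12.5%, against the stated 17%.

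**The case against.** The protocol shows no formula, so the omission of √2 is inferred. On the additive scale, entering 17% gives 83% to 84% and 32 to 34 participants, not exactly 80% and 36. Rounding 34 up to a multiple of the block size of 6 could explain the gap, but the document does not say so. This stands as a caution about how the figure arose. It does not restore the figure, because the stated inputs do not give 80% for the stated endpoint by any route that treats 17% as a single-scan CV.

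The 17% is unpublished and comes from another study, so it may not carry over. This protocol supplies the main meals on the day before each scan, and tighter diet control could reduce the scatter. A CV of 14% would give about 72% power, and 12.5% would give 80%. But the protocol states no lower CV and makes no such argument. If the 17% is really the SD of a change, the section misdescribes it and still needs correcting.

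The protocol also expects that volume may fall in the maltodextrin arm, so the between-arm difference could exceed the 18% uncontrolled pilot increase. That is fair: a detectable difference of 20 points is not out of reach. The power claim, however, is made for 15 points.

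Finally, the design, the endpoint, the test and the type I error are untouched. What is wrong is the stated sensitivity.

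**Conclusion.** The concern holds. On the protocol's own inputs, 36 complete data sets give about 58% one-tailed power for a 15-point difference, not 80%. The range over reasonable scales is 52% to 59%, so 58% is near the top. The chance of missing a true 15-point effect is about 42% rather than 20%, and the difference detectable with 80% power is about 20 points.

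This rests on three assumptions: the 17% is, as worded, the CV of a single fasting volume and carries over to this trial; errors at the two visits are independent; and everyone in an arm has the same true response. Variation in response between people would lower power further. Positively correlated errors between the visits would raise it, but the protocol claims none. The one-tailed test is taken as given and is not the source of the discrepancy.

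**What to change.** Keep 36 and correct the power statement in Sample Size and justification. Suggested wording:

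> The SD of the percentage change is taken as √2 × 17% = 24%, assuming independent within-person errors at the two scans. With 36 complete data sets (18 per arm) and a one-tailed alpha of 0.05, the t-test has about 58% power for a 15-point difference between arms (about 52% to 54% if volumes are treated as lognormal) and 80% power for a difference of about 20 points.

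If the 17% was in fact an SD of change, or if a lower CV is expected under the controlled meals, say so and give the source.

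If a baseline-adjusted analysis were adopted in place of the t-test on change, quote its power instead. With residual SD 17 × √(1 + r), where r is the correlation between baseline and follow-up volume, power at 15 points would be about 61% for r = 0.8 and 71% for r = 0.4. These correlations are assumptions, as the protocol gives none.

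The cost is one paragraph and a less favourable stated power. No extra participants are needed unless the sponsor wants 80% power at 15 points, which would take about 66.

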### **Assessment of Efficacy**

| Primary endpoint                         | Outcome Measure                                                    |
|-------------------------------------------------|---------------------------------------------------------------------------|
| Percentage change in fasting colonic volume     | Difference in mean response between arms                                  |
| Secondary endpoints                      | Outcome Measure                                                    |
| Change in whole gut transit time                | Difference between treatment arms by ranking, unless normally distributed |
| Percentage change in fasting colonic gas volume | Difference in mean response between arms                                  |
| Change in fasting breath hydrogen               | Difference in mean response between arms                                  |
| Change in fasting breath methane                | Difference in mean response between arms                                  |

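### A normality check on the trial data may move the primary endpoint to an unnamed non-parametric test, although its stated outcome measure is a difference in means

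*Protocol*

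**What the plan says.** The analysis rule is the last paragraph of the protocol's *Sample Size and justification* section. It has four steps:

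- It opens with the check itself: "Data will be assessed for normality using the Shapiro-Wilk test and other such methods as appropriate".
- Next comes the route for data that pass: "Where normally distributed, endpoints will be assessed using parametric methods".
- A third sentence picks out the main comparison and names a test for it: "The primary outcome measure will be analysed by t-test to compare the primary" (its remaining words say only that the two arms are compared).
- It closes with the route for data that fail: "Where the data is not normally distributed, non-parametric methods will be used".

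The primary endpoint is "Percentage change in fasting colonic volume after one week of dietary intervention as measured by MRI". In the *Assessment of Efficacy* table its outcome measure is "Difference in mean response between arms", with no condition attached. The transit-time row is the only one that allows another approach: "Difference between treatment arms by ranking, unless normally distributed".

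The protocol gives no threshold for the normality check and does not say whether it is applied per arm or to pooled data. It names no non-parametric method, and gives no effect measure for the primary endpoint if that route is taken.

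**The concern.** The t-test sentence for the primary endpoint stands between two conditional sentences, and nothing exempts that endpoint from the condition. The primary test would therefore be settled by looking at about 18 values per arm, with an open clause about further methods of checking.

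What is at stake is the meaning of the primary result. A rank test such as Mann-Whitney compares the ordering of values between arms and does not estimate a difference in means. One of the two permitted routes would thus leave the trial without the quantity that its own table promises. The choice between routes could also decide whether the result is declared significant.

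**Working it through.** **1. Reproduce the sample size.** Inputs from *Sample Size and justification*: 36 participants randomised 1:1 (18 per arm), 80% power, a 15% difference, one-tailed alpha 0.05, within-individual coefficient of variation 17%. Formula: n per arm = 2 × [(1.645 + 0.842) × SD / difference]².

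- Percentage scale, SD 17, difference 15: n = 15.9, so 16 per arm. With the t distribution it is 17 per arm (34 in total). Power at 18 per arm is 0.83.
- Log scale, SD = √ln(1 + 0.17²) = 0.169, difference = ln 1.15 = 0.140: n = 18.04, which is 36 in total unrounded or 38 rounded up. Power at 18 per arm is 0.785.

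Both routes land within two participants of 36, and both compare means. The paragraph says nothing of an allowance for a rank test.

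**2. Compare the text with the table.**

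| Endpoint | Method under the text | Outcome measure in the table |
|---|---|---|
| Colonic volume (primary) | t-test if normal, otherwise non-parametric | Difference in means, no condition |
| Transit time | Parametric if normal, otherwise non-parametric | Ranking unless normal |

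Text and table agree for transit time. For the primary endpoint they agree only if the data pass the normality check.

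**3. How often would the switch occur, and what would it do?** The protocol gives neither the rule nor the distribution, so these are assumptions: Shapiro-Wilk at 0.05 in each arm; Mann-Whitney if either arm fails, otherwise the t-test; one-sided 0.05; 18 per arm; 6,000 simulated trials per scenario. The log-SD of 0.239 is √2 × 0.169, the value if 17% is the variation of a single measurement and not of the change.

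| Data | Switch | Null rejection: two-stage / t-test | Power at 15%: two-stage / t-test / Mann-Whitney |
|---|---|---|---|
| Normal, SD 17 | 10% | 0.048 / 0.045 | 0.828 / 0.830 / 0.807 |
| Log-normal ratio, log-SD 0.169 | 20% | 0.051 / 0.050 | 0.779 / 0.779 / 0.757 |
| Log-normal ratio, log-SD 0.239 | 29% | 0.056 / 0.053 | 0.532 / 0.525 / 0.509 |

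The 10% for normal data is the false-alarm rate of testing two arms: 1 − 0.95² = 0.0975. The simulation standard error of a 5% rejection rate is √(0.05 × 0.95 / 6000) = 0.0028, so the null rates sit close to nominal.

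**4. Do the two tests reach the same conclusion?** With a true 15% effect, the t-test and Mann-Whitney disagree on significance in about 6% (log-SD 0.169) to 9% (log-SD 0.239) of trials. That counts all trials, whether or not the check fails. Repeating the simulation, the trials in which the assumed rule switches and the two tests also disagree are about 2% and 4% respectively. The larger figures apply to a choice left open, the smaller ones to the strict rule assumed here.

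**The case against.** **The intended analysis may simply be the t-test.** The protocol names it for the primary endpoint, and the table confines ranking to transit time. That is a plausible reading. But the sentence on non-parametric methods follows directly and is general, so the text is at best ambiguous.

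**A rank test is an inference.** The protocol says only that the methods are non-parametric, and a permutation test on means would keep the stated measure. This is correct. The ranking wording for transit time makes a rank test the likelier meaning, but the mismatch depends on that reading.

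**Analysts are blind.** *Randomisation and Blinding* keeps analysts blind until the primary and secondary analyses are complete, so a test could hardly be picked to favour one arm. That limits the discretion. It does not remove the dependence on the data or the mismatch with the table.

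**The sample size would still serve a rank test.** Dividing 17 per arm by 0.955, the efficiency of Mann-Whitney relative to the t-test for normal data, gives 17.8, or 18 per arm, and its simulated power with SD 17 is 0.807. The planned number is therefore not inadequate for that route. The point is what the test estimates.

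**Stronger readings that do not hold.** A reader might infer that the pre-test inflates type I error or costs power. With the same shape in both arms it does neither to any material extent. A rejection rate of 10.1% against 6.5% for the t-test appears when equal means are paired with a normal arm and a left-skewed exponential arm, but nothing in the protocol suggests such shapes. Nor should the higher power of a baseline-adjusted log model be counted as the cost of the switch, since that gain comes mainly from the adjustment.

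**Conclusion.** The point stands as an inconsistency in how the primary analysis is fixed. The text allows a non-parametric primary test; the table promises a difference in means whatever the data look like. Under the natural reading, one permitted route does not deliver the stated outcome measure.

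Its practical size is modest. The switch rate of 10 to 29% rests on the assumed rule and distributions, and the 29% further requires the 17% to be inflated by √2, so it does not follow from the protocol alone. The conclusion would differ between the two tests in a minority of trials, and the average error rates are almost unaffected. The point deserves correction because it concerns the primary result and is cheap to settle. It is not a detail properly left to an analysis plan, because the protocol itself states the rule.

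**What to change.** Remove the normality-driven switch for the primary endpoint in *Sample Size and justification* and state one mean-based analysis in advance. Two options fit the present table:

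- the t-test already named, used whatever the normality check shows; or
- preferably, a linear model of percentage change in colonic volume with treatment arm and baseline colonic volume, which is already measured at Visit 3.

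Report the difference in means with its confidence interval. Name one rank or permutation test as a sensitivity analysis only, and use residual plots as a check that does not change the primary method.

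A log-scale model is optional. If it is chosen, the *Primary endpoint* and *Assessment of Efficacy* entries must be reworded to a ratio between arms, or a new mismatch replaces the old one.

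The cost is wording in the protocol, settled before unblinding. No new data are needed, and the planned number of 36 does not change.

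### The primary t-test on percentage change is valid but wastes baseline information already collected; log-scale ANCOVA would be more precise unless baseline and follow-up volumes are very highly correlated

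*Protocol*

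**What the plan says.** The Primary endpoint section gives "Percentage change in fasting colonic volume after one week of dietary intervention as measured by MRI". Under Sample Size and justification, the analysis paragraph says "The primary outcome measure will be analysed by t-test to compare the primary" endpoint between the groups, after a Shapiro-Wilk check. It adds: "Where the data is not normally distributed, non-parametric methods will be used". The Assessment of Efficacy table pairs "Percentage change in fasting colonic volume" with "Difference in mean response between arms".

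No baseline covariate, log transformation or ANCOVA appears in the protocol, and the unnamed non-parametric fallback carries no baseline adjustment either. Colonic volume is measured by MRI at Visit 3 (Day 8), before the first supplement serving, and again at Visit 5 (Day 15). Randomisation is 1:1 in blocks of 6, with no stratification mentioned, and 18 participants per group are planned.

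**The concern.** Apart from the scale, a comparison of change from baseline is a comparison of follow-up with the baseline coefficient fixed at 1. When the baseline is itself noisy, the best-fitting coefficient is below 1. The protocol reports a "within-individual coefficient of variation for fasting colonic volume of 17% (unpublished"), so one scan is a noisy measure of a person's usual volume: a low first scan tends to be followed by a rise and a high one by a fall.

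Fixing the slope at 1 over-corrects for baseline. Two things follow: the estimate is less precise than the data allow, and the estimated effect depends on which arm happened to start with larger volumes. With 18 per arm, both matter. Because the protocol names the test and the scale, this is a stated choice and not a detail left open for a later plan.

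**Working it through.** **Inputs from the protocol.** 18 per arm; one-sided alpha 0.05; target difference 15%; CV 17%.

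**Input not in the protocol.** The correlation rho between Day 8 and Day 15 log volumes. A range of 0.4 to 0.9 is assumed, with equal variances at the two visits and log-normal volumes.

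**1. The plan's own figure.** The protocol states: "A sample size of 36, randomised 1:1, would give 80% power to detect a 15% increase in the change in volume between treatment arms". On the log scale, delta = ln(1.15) = 0.1398 and SD = √ln(1 + 0.17²) = 0.1688. The standardised effect is 0.1398 / (0.1688 × √(2/18)) = 2.484. Then 2.484 − 1.645 = 0.839, which gives power 79.9% (78.5% by the noncentral t). The stated 80% is therefore reproduced if 17% is read as the SD of the *change*. If 17% is the CV of *each scan*, the SD of the change is 0.1688 × √2 = 0.2387. The standardised effect is then 1.756 and power 54.4% (53.1% by the noncentral t). Which reading is right is a separate question, so both are carried below.

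**2. Variance of ANCOVA relative to change.** With variance σ² at each visit:

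- change score: 2σ²(1 − rho)
- ANCOVA residual: σ²(1 − rho²)
- ratio: (1 + rho)/2

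Estimating the slope with 36 participants multiplies the ratio by 1 + 1/(36 − 4) = 1.031.

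| rho | (1 + rho)/2 | × 1.031 | Variance reduction |
|---|---|---|---|
| 0.4 | 0.70 | 0.722 | 28% |
| 0.5 | 0.75 | 0.773 | 23% |
| 0.7 | 0.85 | 0.877 | 12% |
| 0.8 | 0.90 | 0.928 | 7% |
| 0.9 | 0.95 | 0.980 | 2% |
| 0.94 | 0.97 | 1.000 | none |

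**3. Power by simulation.** 20,000 trials per scenario, 18 per arm, true ratio 1.15, one-sided 0.05.

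| rho | 17% = CV of each scan: % change t-test → log-ANCOVA | 17% = SD of change: % change t-test → log-ANCOVA |
|---|---|---|
| 0.4 | 52% → 65% | 78% → 89% |
| 0.5 | 53% → 63% | 79% → 87% |
| 0.7 | 52% → 57% | 78% → 83% |
| 0.8 | 52% → 55% | 78% → 81% |
| 0.9 | 52% → 54% | 79% → 80% |

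The noncentral t gives 79.2% for ANCOVA in the last cell. With no true effect, both methods rejected in about 5% of trials.

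**4. Sensitivity to chance imbalance.** With 17% as the CV of each scan, the SD of log baseline is 0.1688/√(1 − rho), and the SE of the between-arm baseline difference is that times √(2/18) = 1/3. Change from baseline leaves a fraction (1 − rho) of the difference uncorrected, so a one-SE imbalance shifts the estimate by 0.1688 × √(1 − rho)/3:

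- rho 0.4: 0.0436 on the log scale
- rho 0.9: 0.0178 on the log scale

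On the percentage-change scale, the simulated shift is 4.9 points at rho 0.4 and 2.0 points at rho 0.9. If 17% is the SD of the change, it is 3.4 and 1.4 points. The correlation of the percentage-change estimate with the baseline difference ran from about −0.55 (rho 0.4) to −0.22 (rho 0.9). For ANCOVA it was about 0.

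**The case against.** The strongest reply is that nothing here is an error. In a randomised trial, a t-test on change is valid and unbiased on average. This stands: the point is about efficiency and about bias conditional on the observed baselines.

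Several stronger readings are tempting, and the protocol does not support them.

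- *The t-test ignores baseline.* It does not. Change from baseline already removes a fraction rho of any imbalance; only the remaining (1 − rho) is at issue.
- *Percentage change is so skewed that the test suffers.* In simulation, a t-test on log change gained only about 1 power point over one on percentage change. The benefit comes from estimating the baseline slope, and the log scale alone adds little.
- *A large gain is assured.* It depends on rho, which the protocol does not report. At rho 0.8 to 0.9 the gain is about 1 to 3 power points, and it disappears near 0.94.
- *The trial has only 52% power, so the t-test is untenable.* That figure follows from one reading of the 17%, which is a separate matter. The advantage of ANCOVA holds under either reading, but it does not restore 80% power at 18 per arm under the less favourable one.

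Another objection is that a separate analysis plan might add the covariate. It might, but the protocol names an unadjusted test and a mean-difference outcome measure, so such a plan would depart from it.

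**Conclusion.** The point holds as a free improvement. The planned test is sound in type I error but less precise than the collected data allow, and its estimate moves with chance baseline differences. Over assumed rho 0.4 to 0.9, log-ANCOVA adds about 13 to 2 power points if 17% is the CV of each scan, and about 11 to 1 if it is the SD of the change. A one-SE baseline imbalance leaves about 2 to 5 percentage points in the planned estimate when the within-person CV is 17%.

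The direction is secure for any rho below about 0.94; the size is not, because rho is unknown. The figures assume log-normal volumes with equal variance at both visits. A reader might infer that ANCOVA makes the result wholly free of imbalance. It removes the linear dependence on log baseline volume and nothing more.

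**What to change.** Make the primary analysis a linear model of log(Day 15 colonic volume) on arm and log(Day 8 colonic volume). Report the adjusted geometric-mean ratio, oligofructose to maltodextrin, back-transformed to a percentage, with its confidence interval.

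Three pieces of text need to change with it:

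- Reword the primary outcome measure in the Assessment of Efficacy table from a difference in means to this ratio.
- For the primary endpoint, use this model in place of the normality-dependent choice between the t-test and an unnamed non-parametric test.
- Keep mean percentage change per arm as a descriptive summary.

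For the secondary endpoints, add the baseline value as a covariate on a scale suited to each variable. The log form should not be carried over automatically: the transit score averages the positions of five markers over eight bowel sections and is already planned for ranking, so a rank-based adjustment would fit it better. Breath gas readings may be at or near zero, where a log fails.

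The cost is one degree of freedom, a reworded effect measure and edits to the text. No extra participants, visits or scans are needed.
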